### 8.2.2 Treatment management for patients receiving CAPOX

Capecitabine dose modifications for patients treated with CAPOX are detailed in Table 8.2.2.2. See Tables 8.2.1.2 and 8.2.1.3 for oxaliplatin-specific toxicities. Dose modifications are based on the dose level changes outlined in Table 8.2.2.1.

Additionally, the following dose modification instructions must be followed:

All dose modifications should be based on the adverse event requiring the greatest dose modification.

If capecitabine is held or discontinued, oxaliplatin continues per protocol unless otherwise contraindicated.

Capecitabine and oxaliplatin doses that have been reduced may not be escalated.

Table 8.2.2.1. CAPOX (capecitabine per day in two divided doses) dose levels

|                     | Dose Level 0
Starting Dose
(mg/m  /d) | Dose Level -1
(mg/m  /d) | Dose Level -2
(mg/m  /d) | Dose Level -3 |
|---------------------|-----------------------------------------------------------------------|------------------------------------------------|------------------------------------------------|----------------------|
| Oxaliplatin  | 130                                                                   | 100                                            | 85                                             | Discontinue          |
| Capecitabine | 2000                                                                  | 1500                                           | 1000                                           | Discontinue          |

Table 8.2.2.2. Treatment management for capecitabine (See Tables 8.2.1.2 and 8.2.1.3 for oxaliplatin-specific toxicities.)

|                                                                                                                                                                                                                                                                                                                                                                                                                                                             |                                    |
|-------------------------------------------------------------------------------------------------------------------------------------------------------------------------------------------------------------------------------------------------------------------------------------------------------------------------------------------------------------------------------------------------------------------------------------------------------------|------------------------------------|
| Important table instructions:                                                                                                                                                                                                                                                                                                                                                                                                                 |                                    |
| 
 
• Dose modifications for capecitabine are based on the dose level changes on Table 8.2.2.1.
 
• Hold capecitabine until any AE requiring dose modification returns to ≤ grade 1 unless indicated otherwise in the treatment management sections/tables. If recovery to ≤ grade 1 (or to other level specified) has not occurred after 3 weeks of delay, study therapy must be discontinued.
 
 |                                    |
| CTCAE v5.0                                                                                                                                                                                                                                                                                                                                                                                                                                                  | Modifications for AEs that         |
| Adverse Event/Grade                                                                                                                                                                                                                                                                                                                                                                                                                                         | REQUIRED DELAY IN TREATMENT |

|                                                                                              |                                                                                                                                            |
|----------------------------------------------------------------------------------------------|--------------------------------------------------------------------------------------------------------------------------------------------|
| Neutrophil count decreased:
Grades 2 (ANC 1000-1500/mm  ), 3, 4 | Hold until <math>\geq 1500/\text{mm}^3</math>. If recovery takes:
1 wk – maintain dose;
2-3 wks – ↓ one dose level            |
| Platelet count decreased:
Grades 2, 3                                       | Hold until <math>\geq 75,000/\text{mm}^3</math>
If recovery takes:
1 wk – maintain dose;
2-3 wks – ↓ one dose level |
| Grade 4                                                                                      | Hold until <math>\geq 75,000/\text{mm}^3</math>
↓ one dose level                                                                 |

Table 8.2.2.2. Treatment management for capecitabine (*continued*)

| CTCAE v5.0
Adverse Event/Grade                                                         | Modifications for AEs that
REQUIRED DELAY IN TREATMENT                                                                                                                                                                                                                                            |
|-------------------------------------------------------------------------------------------|------------------------------------------------------------------------------------------------------------------------------------------------------------------------------------------------------------------------------------------------------------------------------------------------------|
| Grade 1                                                                                   | Maintain dose level                                                                                                                                                                                                                                                                                  |
| Grade 2                                                                                   | Treatment must be held until resolved to grade 0 or 1 to avoid severe complications.
1 st occurrence – Maintain dose level
2 nd occurrence – ↓ one dose level
3 rd occurrence – ↓ one dose level
4 th occurrence – discontinue |
| Grade 3                                                                                   | Treatment must be held until resolved to grade 0 or 1 to avoid severe complications.
1 st occurrence – ↓ one dose level
2 nd occurrence – ↓ one dose level
3 rd occurrence – discontinue                                                     |
| Grade 4                                                                                   | Discontinue permanently OR if the physician deems it to be in the patient's best interest to continue, interrupt until resolved to grade 0 – 1.
↓ two dose levels                                                                                                                                 |
| * Determination of "clinically significant" AEs is at the discretion of the investigator. |                                                                                                                                                                                                                                                                                                      |

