## 8.2 Dose Modifications

The CTCAE v5.0 must be used to grade the severity of AEs. Refer to [http://ctep.cancer.gov/protocolDevelopment/electronic\\_applications/ctc.htm](http://ctep.cancer.gov/protocolDevelopment/electronic_applications/ctc.htm).

Deviations from the recommended treatment modifications/management must be documented in the patient treatment record.

In the event of disease recurrence, second primary colorectal cancer, or diagnosis of an invasive second primary/secondary malignancy, study therapy will be discontinued; further therapy is at the investigator's discretion. Tests, exams, and assessments **are required** and patients will continue to be followed off treatment for vital status per protocol.

If, in the opinion of the investigator, a toxicity is considered to be due solely to one component of the study treatment (i.e., 5-FU, capecitabine, oxaliplatin, or irinotecan) and the dose of that component is held or modified in accordance with the guideline below, the other components may be administered per protocol guidelines.

If several toxicities with different grades of severity occur at the same time, the dose modifications should be according to the highest grade observed.

Any chemotherapy doses that have been reduced may not be escalated.

**For any concomitant conditions apparent at baseline, the dose modifications will apply according to the corresponding shift in toxicity grade, if the investigator feels it is appropriate.** For example, if a patient has Grade 1 asthenia at baseline that increases to Grade 2 during treatment, this will be considered a shift of one grade and treated as Grade 1 toxicity for dose-modification purposes only.

**For specific questions or concerns regarding this section, please contact [name] [[contact]](mailto:[contact]) and/or [name] [mailto:[name]\\[contact]](mailto:[contact]).**  
In the event of treatment-related AEs during consolidation chemotherapy that requires treatment hold for  $\geq 30$  days from the date of the planned cycle, consolidation chemotherapy should be discontinued. If consolidation chemotherapy is discontinued because of delay, patients the subject should be referred for presurgical restaging as detailed in the study calendar in section 5.0

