In the event of non-treatment related AEs that result in dose delays of 30-60 days and have resolved to grade  $\leq$  grade 1 by 60 days from the date of the planned cycle, patients may continue with consolidation chemotherapy if deemed in their best interest by the treating oncologist.

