- a** Chemotherapy should not proceed with  $\geq$  grade 3 anemia. Transfusion is acceptable for improving the hemoglobin value to allow therapy to continue without delay. The patient should be assessed to rule out other causes of anemia. *Use of erythropoiesis-stimulating agents is discouraged.*
- b** Resolved means that all clinically significant AEs are  $\leq$  grade 1 (except bilirubin, which must be  $\leq$  the baseline grade) on Day 1 of the next scheduled cycle (i.e., treatment can be given without delay).
- c** Hold and check weekly. ***With exception of bilirubin, resume treatment when toxicity is  $\leq$  grade 1.*** If toxicity has not resolved after 4 weeks of delay, discontinue mFOLFOX6
- d** Determination of "clinically significant" AEs is at the discretion of the investigator.

Table 8.2.1.3. Treatment management for oxaliplatin-specific toxicities

| Nervous System Disorders                                                           |                                                                                                                                                           |                                                                               |
|------------------------------------------------------------------------------------|-----------------------------------------------------------------------------------------------------------------------------------------------------------|-------------------------------------------------------------------------------|
| Paresthesias/Dysesthesias/
Neuropathy (Peripheral
motor; Peripheral sensory) | 1-7 day duration
(intermittent or continuous)                                                                                                          | > 7 day duration a
(intermittent or continuous)                 |
| Grade 1                                                                            | Maintain dose                                                                                                                                             | Maintain dose                                                                 |
| Grade 2                                                                            | Maintain dose a                                                                                                                                | Decrease oxaliplatin one dose level a                |

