| 
a Chemotherapy should not proceed with <math>\geq</math> grade 3 anemia. Transfusion is acceptable for improving the hemoglobin value to allow therapy to continue without delay. The patient should be assessed to rule out other causes of anemia. Use of erythropoiesis-stimulating agents is discouraged.
 
b Resolved means that all clinically significant AEs are <math>\leq</math> grade 1 (except bilirubin, which must be <math>\leq</math> the baseline grade) on Day 1 of the next scheduled cycle (i.e., treatment can be given without delay).
 
c Hold and check weekly. With exception of bilirubin, resume treatment when toxicity is <math>\leq</math> grade 1. If toxicity has not resolved after 4 weeks of delay, discontinue mFOLFIRINOX.
 
d If multiple episodes of grade 2 diarrhea occur during the cycle but do not delay the subsequent cycle, irinotecan may be decreased one dose level at the discretion of the investigator.
 
e Determination of "clinically significant" AEs is at the discretion of the investigator.
 |                  |                  |

Table 8.2.3.2. Treatment management for mFOLFIRINOX (*continued*)

| Nervous System Disorders                                                              |                                                                                                                                                      |                                                            |
|---------------------------------------------------------------------------------------|------------------------------------------------------------------------------------------------------------------------------------------------------|------------------------------------------------------------|
| Paresthesias/Dysesthesias/
Neuropathy (Peripheral
motor; Peripheral
sensory) | 1-7 day duration
(intermittent or continuous)                                                                                              | > 7 day duration
(intermittent or continuous)    |
| Grade 1                                                                               | Maintain dose                                                                                                                                        | Maintain dose                                              |

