#### 8.2.4 Treatment Management of Patients on Chemoradiation\*

For management of capecitabine or 5-FU related toxicities, please see Table 8.2.2.2 ([Section 8.2.2](#)).

Table 8.2.4.1: Dose levels for capecitabine during chemoradiation

|              | Dose Level 0
Starting Dose
(mg/m  /d) | Dose Level -1
(mg/m  /d)         | Dose Level -2
(mg/m  /d)        | Dose Level -3
(mg/m  /d) |
|--------------|---------------------------------------------------------|-------------------------------------------------|------------------------------------------------|-----------------------------------------|
| Capecitabine | 1650 per day in two divided doses on days of RT         | 1240 per day in two divided doses on days of RT | 930 per day in two divided doses on days of RT | Discontinue                             |

Table 8.2.4.2: Dose levels for 5-FU during chemoradiation

|                                                                                                           | Dose Level 0
Starting Dose
(mg/m  ) a | Dose Level -1
(mg/m  ) a | Dose Level -2
(mg/m  ) a | Dose Level -3
(mg/m  ) |
|-----------------------------------------------------------------------------------------------------------|--------------------------------------------------------------------|----------------------------------------------------|----------------------------------------------------|---------------------------------------|
| Infusional 5-FU                                                                                           | 225 mg/m  iv continuous infusion                       | 170 mg/m  iv continuous infusion       | 125 mg/m  iv continuous infusion       | Discontinue                           |
| a: continuous infusion Monday-Friday on radiation days or 7 days per week based on preference of the site |                                                                    |                                                    |                                                    |                                       |

**\*NOTE: If in the opinion of the investigator, a toxicity is considered to be due solely to the radiation, then the radiation can be held at the investigator's discretion. The rationale for treatment break and the duration of the**

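### Section 8.2 gives contradictory instructions on what stops, and when, after a prolonged chemotherapy hold, and Section 8.2.4 carries one of them into chemoradiation

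*Combined protocol and SAP*

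**What the plan says.** All of the following is current protocol text, not the summary of changes.

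- **Section 8.2, treatment-related events.** When a hold reaches 30 days "from the date of the planned cycle, consolidation chemotherapy should be discontinued".
- **Section 8.2, unrelated events.** For "non-treatment related AEs that result in dose delays of 30-60 days", the patient may continue consolidation if the event has settled to grade 1 or less by day 60 and the oncologist judges it in the patient's interest.
- **Tables 8.2.1.2 and 8.2.3.2, footnote c.** "If toxicity has not resolved after 4 weeks of delay, discontinue mFOLFOX6" and "If toxicity has not resolved after 4 weeks of delay, discontinue mFOLFIRINOX".
- **Section 8.2.2, text (CAPOX).** "If capecitabine is held or discontinued, oxaliplatin continues per protocol unless otherwise contraindicated".
- **Table 8.2.2.2, instructions (capecitabine).** If recovery to grade 1 or less, or to another stated level, "has not occurred after 3 weeks of delay, study therapy must be discontinued". Dose changes are taken from Table 8.2.2.1.
- **Section 8.2.4 (chemoradiation, both arms).** "For management of capecitabine or 5-FU related toxicities, please see Table 8.2.2.2". The section then prints its own dose levels in Tables 8.2.4.1 and 8.2.4.2.
- **Section 7.2.** Consolidation may start up to 4 weeks after radiation when side effects are more severe. Longer delays are discussed with the study PI.

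**The concern.** These are patient-level stopping instructions, and a site may find two that apply to one patient and disagree. One choice ends therapy that the protocol elsewhere continues; the other continues therapy past a stated stop.

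The statistical interest is indirect. Assignment is made at registration, before chemoradiation, so the choice between passages is made after randomization. The outcome enters three places in Section 13:

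- the early-off-treatment (EOT) comparison in 13.5.1, which counts patients who start consolidation and stop early for toxicity, among other reasons;
- the mITT population of the phase II primary test, which requires completed chemoradiation and at least one dose of consolidation chemotherapy;
- the per-protocol population, which requires at least three cycles.

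Unclear stopping rules add variation to all three that has nothing to do with the regimens.

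**Working it through.** The plan states no figure on this point, so the check sets the passages side by side. Limits in days: 3 × 7 = 21, 4 × 7 = 28, and 30 as written. I read *after 3 weeks* and *after 4 weeks* as from day 21 and day 28; a stricter reading moves each boundary by one day.

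**1. Within CAPOX.** From day 21 without recovery, Table 8.2.2.2 ends study therapy, while the 8.2.2 text keeps oxaliplatin going when capecitabine is held or stopped. The two agree only if *study therapy* means capecitabine alone. Section 8.2 uses the same phrase for the whole treatment: on recurrence or a second malignancy, study therapy ends and further treatment is at the investigator's discretion.

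**2. Tables against the general rules.** What each passage requires for an event that is still unresolved:

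| Day of hold | Table 8.2.2.2 (CAPOX) | Footnote c (mFOLFOX6, mFOLFIRINOX) | Section 8.2, treatment-related | Section 8.2, not treatment-related |
|---|---|---|---|---|
| up to 20 | no stop | no stop | no stop | no stop |
| 21–27 | stop | no stop | no stop | no stop |
| 28–29 | stop | stop | no stop yet | no stop |
| 30–60 | stop | stop | stop | may continue if grade ≤1 by day 60 |

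For a treatment-related event in one mFOLFOX6 or mFOLFIRINOX patient, the table and Section 8.2 differ on days 28 and 29 only. For an unrelated event they differ over the whole 30 to 60 day range. The CAPOX 3-week rule meets the same allowance and differs from it over the same range. Neither table makes an exception by attribution, and no sentence says whether the table or Section 8.2 governs.

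**3. Chemoradiation.** Section 8.2.4 sends capecitabine and 5-FU toxicity to Table 8.2.2.2. Taken literally, this has two effects.

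- *Stop rule.* A 3-week hold during chemoradiation ends study therapy before consolidation begins. Section 7.2 points the other way, since it provides for a late start of consolidation after more severe effects.
- *Dose levels.* Table 8.2.2.2 refers to Table 8.2.2.1, with capecitabine at 2000, 1500 and 1000 mg/m²/d. Table 8.2.4.1 gives 1650, 1240 and 930. From the 1650 start, one level down is 1500 by the first table (1500/1650 = 0.909, a 9% reduction) and 1240 by the second (1240/1650 = 0.752, a 25% reduction). Table 8.2.2.1 has no 5-FU row.

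**4. Route into the analysis.** A stop during consolidation counts toward the EOT rate and, if it comes before the third cycle, removes the patient from the per-protocol set. A stop during chemoradiation removes the patient from mITT and from the EOT denominator. Phase III tests DFS on ITT, whose membership is fixed at randomization.

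**The case against.** Much of the opposing case stands.

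- **Three limits are not in themselves an error.** A reader might infer that having 3 weeks, 4 weeks and 30 days in one protocol, so that one toxicity ends therapy under CAPOX but not under mFOLFOX6, is a fault. The documents do not support that. CAPOX runs in 3-week cycles and the other two regimens in 2-week cycles, so limits of one and two cycles may be deliberate.
- **The 28- against 30-day gap is narrow.** Footnote c has sites check weekly, and a stricter table can sit beneath an outer cap. Stopping at 4 weeks breaches nothing in the 30-day rule. The 30 to 60 day allowance is harder to fit, because it permits what the tables rule out.
- **Footnote c speaks of toxicity.** That might be meant for treatment-related events only. But the table columns refer to adverse events with no condition on attribution, and Table 8.2.2.2 covers any event requiring dose modification.
- **The single-component rule in 8.2 is permissive.** It says the other drugs may be given under protocol guidelines, and the tables are those guidelines. It does not contradict the 3-week stop.
- **No safety breach is shown.** A reader might infer that patients would be dosed through unresolved toxicity. The tables generally require recovery to grade 1 or less, or another stated level, before treatment resumes.
- **No bias in mITT is shown.** The chemoradiation rules are the same in both arms, and only patients with fluoropyrimidine toxicity are referred to Table 8.2.2.2.
- **The dose tables are labelled.** Table 8.2.4.1 is titled for chemoradiation and Table 8.2.2.1 for CAPOX, so most sites would probably find the former. The cross-reference still leads to the latter.

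The conflict within 8.2.2 can be softened by reading *study therapy* narrowly or by letting *per protocol* absorb the 3-week rule. Neither reading is stated.

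**Conclusion.** The point holds as an internal inconsistency in the treatment-hold instructions, in three parts: the 8.2.2 text against Table 8.2.2.2; the table limits against the 30-day and 30 to 60 day rules of Section 8.2, with no precedence stated; and the 8.2.4 cross-reference, which brings a 3-week study-therapy stop and the CAPOX dose levels into chemoradiation. It rests on reading *study therapy* as Section 8.2 uses it and on the tables applying whatever the attribution.

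The number of patients affected cannot be derived from the documents, nor can the direction of any effect on the EOT, mITT or per-protocol comparisons. CAPOX is an investigator's choice in the control arm only, so its 3-week rule in consolidation acts on one arm. That shows a route to imbalance, not its size. Phase III ITT membership is unaffected. The correction should be made because the instructions conflict and the remedy is cheap, not because a bias has been demonstrated.

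**What to change.** In one amendment, reconcile Section 8.2, Section 8.2.2 with Table 8.2.2.2, footnote c of Tables 8.2.1.2 and 8.2.3.2, Section 8.2.4, and the start-of-consolidation text in 7.2. For each regimen and, separately, for chemoradiation, state:

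- which hold limit governs, and how it relates to the 30-day and 30 to 60 day rules;
- what stops at the limit: the held drug, the regimen, or all study therapy;
- which dose-level table applies;
- whether a patient who reaches the limit during chemoradiation goes on to consolidation.

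The limits need not be equal across regimens. The choice of limit and dose table is the sponsor's. The cost is wording in Section 8.2 and its tables, with a check of 7.2, and no added patients or procedures.
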